### Two-year longitudinal follow-up

Participants will be contacted again two years after the completion of their group sessions. This longitudinal follow-up is ongoing. Participants will be asked to complete a ‘Follow-up Pack’ that will include the same contents as the pre-intervention ‘Welcome Pack’ (mood and sleep questionnaires, saliva collection kit, and an Actiwatch to wear and sleep diary to complete over seven days). Participants will also be asked to take part in a cardiovascular assessment and a clinical diagnostic interview that will explore symptoms experienced since the post-intervention interview. The *Longitudinal Interval Follow-up Evaluation Interview (LIFE-I)* [52] will also be included in the follow-up interview. All researchers conducting two-year follow-up interviews will be blinded to the group that the participants completed.

### Measures

#### Psychopathology measures

 
*Spence Children’s Anxiety Scale (SCAS)* [53] - The SCAS has been shown to be an effective screening instrument for anxiety disorders in the targeted age group. The SCAS is a brief self-report test of anxiety symptoms broadly in line with the dimensions of anxiety disorder proposed by the DSM-IV. The scale assesses six domains of anxiety including generalized anxiety, panic/agoraphobia, social phobia, separation anxiety, obsessive-compulsive disorder and physical injury fears. The SCAS has normative data in the relevant age range and has been shown to have good internal consistency and temporal stability three months apart among 12–15 year olds [54, 55]. This study used the recommended total SCAS cut-offs of >32 for males and >38 for females [45]. 
*Center for Epidemiologic Studies – Depression Scale (CES-D)* [56] - The CES-D is a reliable and well-validated 20-item self-report questionnaire measuring symptoms of depression during the past week [56]. The CES-D has also been validated as a reliable measure for the use in adolescents [57–59]. 
*Kiddie Schedule of Affective Disorders and Schizophrenia Children's Version - Present and Lifetime Version* (K-SADS-PL) [60] – The KSADS-PL is a semi-structured diagnostic interview widely used for research of mood disorder in children and adolescents. It has been shown to be a reliable and valid measure of DSM-IV Axis 1 disorders in this population [61]. The following modules were administered: depression, mania, psychosis, panic disorder, social phobia, specific phobia/agoraphobia, generalised anxiety, obsessive-compulsive disorder, separation anxiety, and post-traumatic stress disorder. Interviews were conducted by trained interviewers and audio recorded. Regular clinical supervision was provided to all interviewers. Approximately 20 % of interviews were double-scored by another interviewer for inter-rater reliability. The *Youth Risk Behavior Survey (YRBS)* [62] assesses health-risk behaviors in youths. Thirty-two items that assess tobacco, alcohol and other drug use were administered. 
*The Child Behavior Checklist, Youth Self Report version (CBCL-YSR)* [63] – The CBCL-YSR is a widely used instrument assessing internalizing and externalizing problem behaviors in young people aged 11 to 18 years. The present study administered the 45-item Externalizing subscale only. 
*Penn State Worry Questionnaire for Children (PSWQ-C) -* The PSWQ–C is a 14-item self-report questionnaire designed to examine the generality, excessiveness and uncontrollability of worry in children and adolescents. It has excellent internal consistency (*α* = .90) and temporal stability (*r* = .92) among 12- to 18-year-olds [64]. 
*Rumination Responses Scale (RRS); subscale of the Response Styles Questionnaire (RSQ-R) -* The RRS is a widely used and well-validated self-report questionnaire that assesses the predisposition to focus on or ruminate on depressed mood. The RRS includes 22 items describing responses to mood that are self-focused, symptom focused and consequence-focused [65]. It has been shown to have adequate psychometric properties with an adolescent sample [66]. 
*General Self-Efficacy Scale (GSES) -* The General Self-Efficacy Scale is a 10-item self-report questionnaire designed to assess a broad and stable sense of personal competence to deal effectively with a wide range of demanding or novel situations [67]. The GSES is widely used and has been shown to have high reliability, stability and construct validity [68].*Longitudinal Interval Follow-up Evaluation Interview (LIFE-I)* [52] The LIFE-I is a semi-structured interview used to assess the longitudinal course of participants’ psychiatric symptoms, mental health treatment and psychosocial functioning.

#### Sleep measures

##### Subjective measures

 
*Sleep Diary* is a widely used sleep questionnaire that collects information on daily sleep onset, morning awakening, and sleep quality. The *Pittsburgh Sleep Quality Index (PSQI) –* the PSQI is a validated self-rated questionnaire used to assess subjective sleep quality and disturbances and the impact of poor sleep on functioning [69]. Adolescent sleep schedules are known to shift dramatically across the week [70]. To explore this shift, the first four questions of the PSQI were altered to include a rating for sleep during the week (i.e., Monday-Friday) as well as a separate rating for weekend (i.e., Saturday-Sunday). This study used the cut-off of a total PSQI of 5 and above [25]. 
*The reduced Morningness-Eveningness Questionnaire (rMEQ)* - The rMEQ was developed from the original Horne-Ostberg Morningness-Eveningness-Questionnaire [71]. It consists of 5 items from the original questionnaire (Items 1, 7, 10, 18, and 19), which determine individual chronotype on a single scale with minimum and maximum values from 4 to 25, where higher scores indicate a tendency towards morningness. The conventional classification for the scores are from 4–7 (Definitely-Evening), 8–11 (Moderately-Evening), 12–17 (Neither), 18–21 (Moderately-Morning) and 22–25 (Definitely-Morning) [72]. Although this measure has not been widely used for adolescents, it correlates highly (*r* = 0.90) with the Morningness-Eveningness Questionnaire [73] which has been validated [74] and used in adolescent samples [75]. 
*Dysfunctional Belief and Attitudes about Sleep Scale – 16 (DBAS-16) -* The DBAS-16 is an abbreviated form of the original 30-item DBAS [76] and was designed to assess dysfunctional sleep-related cognitions. The factor structure of the brief form is similar to the original 30-item version, with four factors reflecting a) perceived consequences of insomnia, (b) worry/helplessness about insomnia, (c) sleep expectations, and (d) medication [77]. It has been shown to have good internal consistency (*α* = 0.77 for clinical and *α* = 0.79 for research samples) and temporal stability (*r* = 0.83), and correlates with other self-report measures of insomnia severity, anxiety and depression [77]. 
*Pre-Sleep Arousal Scale (PAS) -* The PAS is a 16-item self-report questionnaire designed to measure cognitive arousal (items 9–16; e.g., “worry about falling asleep”) and somatic arousal (items 1-8; e.g., “cold feeling in your hands, feet or your body in general”) prior to sleep [78]. The PAS is commonly used in adults but has shown good internal consistency in much younger populations (*α* = 0.85; each subscale *α* = 0.75 [79]). PAS scores are able to differentiate clinical from community samples and correlate significantly with anxiety and sleep measures. 
*Paediatric Daytime Sleepiness Scale (PDSS) -* The PDSS is an 8-item self-report questionnaire designed to assess daytime sleepiness in children and adolescents [80]. 
*Sleep Beliefs Scale (SBS) -* The SBS is an 20-item self-report questionnaire designed to assess general beliefs about sleep, including the influence of substances, diurnal behaviours and pre-sleep activities and thoughts on sleep [81]. The SBS is based on the Sleep Hygiene Awareness and Practice Scale (SHAPS) [82, 83], designed for use in clinical and non-clinical populations [84, 85]. The SBS has three factors: (1) sleep-incompatible behaviours, (2) sleep-wake cycle behaviours and (3) thoughts and attitudes about sleep [81]. The total and subscale scores have been shown to have acceptable internal consistency in non-clinical samples (total score *α* = 0.71, subscale *α* range = 0.47–.63) [81].

##### Objective measures

 
*Actigraphy.* Objective sleep was assessed using Actiwatch-64, Actiwatch-L and Actiwatch 2 (Mini-Mitter Company, Sun River, OR, USA) wristwatch monitors of physical activity used to assess sleep-wake patterns in normal environment over extended periods of time. Actigraphy has been well validated and tolerated in adolescent populations [86].

#### Medical history measure

 A medical history questionnaire used in previous studies [87] was administered in interview form, and includes items about chronic or current illnesses, family history of cardiovascular disease, substances consumed on the day, and measures of height, weight and waist circumference.

#### Cardiovascular measures

 
*Blood Pressure:* Blood pressure was measured using a continuous finger blood pressure device (Portapres, Model 2). This apparatus provides continuous assessment of BP using finger cuffs. It also provides an automated height adjustment feature. Maximum (SBP) and minimum (DBP) BP points are identified for each cardiac cycle using a computer algorithm with the points being visually checked and corrected where necessary. In addition a brachial blood pressure measurement was taken using standard automatic brachial blood pressure monitor. 
*Vagal Activity/Autonomic Balance:* Heart rate variability was derived from a three-lead electrocardiograph (ECG). The ECG will be recorded through Meditrace Ag/AgCl spot electrodes. Electrodes were placed on subject’s lower left and lower right rib cage and a third on the right clavicular notch. The right rib cage electrode served as the ground and the remaining two as recording sites. During subsequent analyses R waves were detected using an automated algorithm, allowing IBI to be calculated by the program. The detection of R waves were then visually checked and edited where the automatic detection is incorrect. Power spectrum analysis of the IBI data was conducted to determine autonomic balance. 
*Endothelial Dysfunction:* Endothelial functioning was assessed by measuring the hyperemic response to a 5 min occlusion of the brachial artery. Brachial artery occlusion was achieved using a standard blood pressure cuff, while the vascular response to occlusion release was be measured by Endo-PAT 2000 equipment (Itamar, Israel). All procedures were non-invasive. 
*Inflammatory markers: S*aliva samples were collected from participant to determine the level of IL-1α, IL-1β, TNFα, IL-6, C-reactive protein, using Bioplex assay kits and the Bioplex instrument. Saliva was collected instead of serum as our previous work has shown that levels of inflammatory proteins correlate well in adolescents and importantly, the sensitivity and detection of cytokines was found to be greater in saliva [88]. Participants collected three 2 mL samples (upon awakening, during the afternoon after school and before going to sleep) each day for two consecutive days at their home, via passive drool. Participants were instructed to avoid eating, drinking, taking medications and brushing their teeth at least 30 min prior to collection. They were also instructed to place samples in their home freezer immediately after collection. Samples were returned on ice and placed in -30 °C freezers until time of assay. All samples were kept frozen from collection to time of processing for bio-assay analysis.

### Sample size requirements and power calculation

A power analysis was conducted prior to commencement of the study in order to provide a guide to sample size requirements. Recruitment was school-based using a cluster sampling scheme to optimize the two-gate screening method being employed (remembering, however, that the RCT is not *cluster-based,* because allocation is at the individual level). Calculations were based on feasible differences in treatment effect at follow-up, where attrition will be greatest. We initially estimated power under assumptions of simple random sampling, and then adjustment was made for the design effect exceeding 1 due to the cluster sampling design.

The treatment effect was estimated to result in group differences of 0.45 SDs for continuous outcome measures and an odds ratio of 2.5 for case level depression, based on preliminary published findings [89]. For α = .05, 120 participants *at follow-up* was estimated to provide 80 % power. Pre-post changes due to intervention in the pilot data were significantly larger than these conservative effect size estimates [48].

Based on our previous experience, we conservatively estimated 10 % attrition from baseline to follow-up, implying that 120/0.90 = 134 adolescents would need to be randomly allocated into the two arms of the study (this was close to the 144 individuals actually randomized). We expected 60 % screening agreement, and 16 % to meet screening cut-off criteria (this was also close to the 27 % who actually met screening criteria). It was conservatively estimated that (i) 70 % meeting screening criteria would also meet diagnostic interview criteria (86 % actually did), and (ii) 50 % meeting diagnostic inclusion would participate in the RCT (65 % actually did). The estimated design effect [90] was 1.44 based on an average cluster-size of 9.275, a coefficient of variation for cluster size of 0.25, and an intra-class correlation of 0.05 on continuous outcome measures. The final estimated required sample size at baseline adjusted for design effect and attrition was 1.44 × 134 = 194 adolescents, which corresponded to estimating need to screen at 194/9.275 = 21 schools. The final actual number of schools screened was 23.

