### Randomisation and blinding

After all Phase 1 assessments had been conducted (i.e., the interview and questionnaires, sleep and cardiovascular assessments), eligible participants who consented to participate in the intervention stage of the trial were randomly allocated to receive either the sleep intervention (Sleep SENSE) or the active control group (Study SENSE). A blinded statistician randomised the eligible participants stratified by gender, age and type of anxiety disorder at baseline using a minimisation method available in the MINIM program (SJW E, SJ D, P R. MINIM: minimisation programme for allocating patients to treatment in clinical trials. Unpublished document Department of Clinical Epidemiology, The London Hospital Medical College, London. 1990.) Participants and their guardians were made aware of the content of the group sessions (i.e., study skills vs. sleep skills) but not of the status of each group (i.e., intervention versus control) or the expected outcome of the study. Researchers conducting the post-intervention interviews were also blinded to which group participants had completed.

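### The sample size is multiplied by a school design effect of 1.44 that does not apply to an individually randomised comparison, so the 194 target and 21-school figure are not justified as derived

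*Protocol article*

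**What the plan says.** In the protocol article, under Sample size requirements and power calculation, the planned effects are "group differences of 0.45 SDs for continuous outcome measures and an odds ratio of 2.5 for case level depression", and 120 participants at follow-up are said to give 80% power at alpha 0.05. Ten per cent attrition raises this to 134, which the article describes as the number to be randomised and as close to the 144 actually randomised.

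The section then turns to schools. It states that the trial is not cluster-based "because allocation is at the individual level", but also that "adjustment was made for the design effect exceeding 1 due to the cluster sampling design". The factor is specified in these words: "The estimated design effect [90] was 1.44 based on an average cluster-size of 9.275, a coefficient of variation for cluster size of 0.25", together with "an intra-class correlation of 0.05 on continuous outcome measures". The closing statement is "The final estimated required sample size at baseline adjusted for design effect and attrition was" 1.44 × 134 = 194, which is converted to 21 schools and set beside the 23 screened.

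Randomisation and blinding confirms individual allocation, "stratified by gender, age and type of anxiety disorder at baseline using a minimisation method". School is neither the unit of allocation nor a minimisation factor.

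**The concern.** A design effect built from cluster size and intra-class correlation (ICC) measures the loss of precision when every member of a cluster is in the same arm, or when a single mean or prevalence is estimated from a cluster sample. Neither is what this section powers: it powers a difference between two arms. When pupils of one school can enter either arm, a good or poor school raises or lowers both arm means together and largely drops out of the difference. Sampling through schools therefore does not, by itself, inflate the variance of the treatment contrast by 1.44.

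What is at stake is how the stated requirement is read. The 194 and the 21 schools depend entirely on the factor. Because 134 is also presented as the number to randomise, a reader cannot tell which figure the trial was meant to reach.

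**Working it through.** **Inputs**, all from the sample size section: mean cluster size m = 9.275; coefficient of variation of cluster size CV = 0.25; ICC = 0.05; effect 0.45 SD; alpha 0.05 (sidedness not stated); 120 at follow-up; attrition 10%. Equal allocation is assumed, since no ratio is given.

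**1. Reproducing the stated figures.**
- Design effect = 1 + ((1 + CV²) × m − 1) × ICC = 1 + (1.0625 × 9.275 − 1) × 0.05 = 1.443, matching 1.44.
- 120 / 0.90 = 133.3, rounded up to 134.
- 1.44 × 134 = 192.96, and 1.443 × 134 = 193.3, which rounds up to 194.
- 194 / 9.275 = 20.9, rounded up to 21 schools.

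The arithmetic holds within rounding.

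**2. The factor for the treatment difference.** Simulated with 21 schools, mean size 9.275, CV 0.25, ICC 0.05 and no treatment-by-school variation, with 20,000 replicates per run. The results are ratios of the variance of the arm difference to its value under independent observations:

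| Allocation and analysis | Variance factor |
|---|---|
| Individual allocation, not stratified by school | 0.98 to 1.02 |
| Individual allocation, school fixed effects in the analysis | 1.08 |
| Whole schools allocated to one arm | 1.43 to 1.44 |

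If the arms were exactly balanced within each school, the factor would be 1 − ICC = 0.95. The stated 1.44 belongs to the last row of the table, which is not this design.

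**3. Effect on the target.** Without the school factor, the article's own base gives 1.00 × 134 = 134. The difference is 194 − 134 = 60 adolescents, or 60/194 = 31% of the stated target. Against 134, the 144 randomised is 10 over; against 194 it is 50 short.

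**4. Whether 134 can stand in its place.** For 0.45 SD and 80% power, a two-sided 0.05 test needs 78 per arm (156 in total) and a one-sided test 62 per arm (124). With 60 per arm, power is 69.3% two-sided and 79.4% one-sided. A two-sided base with no design effect would be 156 / 0.90 = 173.3, i.e. 174 at baseline. With 10% attrition and no design effect, two-sided power is about 73% for 144 randomised and 84% for 194.

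**5. Sensitivity to clustering by delivery group.** Both programmes run in groups, and group effects nested within an arm do not cancel. The article gives no ICC for this. Trial status reports 118 participants in nine parallel groups, which could mean nine in all or nine per arm. Using 1 + (118/g − 1) × ICC with an assumed ICC of 0.02 to 0.10:
- g = 18 (mean size 6.56): 1.11 to 1.56, or about 149 to 209 on a base of 134.
- g = 9 (mean size 13.11): 1.24 to 2.21, or about 166 to 296 on a base of 134.

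**The case against.** The strongest reply is that little harm follows. The inflation errs on the safe side, the calculation was offered as a guide before the study began, and screening, randomisation and post-intervention assessment are complete. The article also judges the 144 randomised against 134, not 194, so its own comment on recruitment does not use the factor; only the comparison of 21 with 23 schools does. All of this stands and limits the practical weight of the point. It does not make 1.44 the right factor, and it exposes the second fault: two requirements side by side with no explanation.

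A further reply is that about 1 is model-dependent. Treatment effects that vary by school would add variance, and one delivery group met at its participants' school, so school and group coincide there. This too is fair. The figure covers school clustering only and assumes no such variation, on which the article is silent.

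It could also be argued that 1.44 is reasonable as an allowance for delivery groups, since it lies inside both sensitivity ranges. But it was derived from school size and presented as a correction for school sampling, so the overlap does not justify the derivation.

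**Conclusion.** The school design effect does not belong in the power calculation for this comparison, and 194 adolescents and 21 schools are not justified as derived. From school clustering alone the factor is about 1 (0.98 to 1.08 in simulation) in place of 1.44, which accounts for 60 of the 194. This rests on individual allocation across schools, the article's ICC of 0.05, and no treatment-by-school variation.

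Four stronger readings are tempting, and the document supports none of them:
- *That the sums are wrong.* Every figure reproduces within rounding; the variance model is what is misapplied.
- *That the trial is underpowered because of this factor.* The error is conservative and overstates the need.
- *That 194 is shown to be too large, or that 134 is enough.* The base of 120 reaches about 80% power only with a one-sided test, and group clustering could raise the requirement by an amount the article does not allow to be fixed.
- *That delivery-group clustering has been wrongly left out.* The full protocol or analysis plan, not shown, may deal with it. The ranges given here rest on an assumed ICC and an ambiguous group count, so they are a sensitivity check only.

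**What to change.** Withdraw the 1.44 and the 194 and 21-school figures that depend on it from the sample-size statement, or say plainly that the school factor does not apply to the treatment contrast. State how 134, 144 and 194 relate and which was the requirement. Restate power for the numbers available at two-year follow-up, giving the sidedness of the test. Do not carry 134 forward as the corrected target. If clustering by delivery group is shown, label it as a sensitivity analysis, state how many groups each arm had, and give the assumed ICC with a range.

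The multilevel models planned under Statistical analysis need not change on this account. The cost is a recalculation and some rewording, with no extra participants; the article reports that the main outcomes had not yet been assessed.

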### Trial status

At submission of this article, Phases 1–4 had been completed, such that 118 eligible participants in nine parallel groups have completed the interventions and pre/post assessments. One additional participant completed the SENSE Study control group because of a scoring error at the screening phase, but did not meet eligibility criteria, so will be excluded from future analyses. Two-year follow-up assessments began in June 2015 and will be completed by December 2016, as such, the main outcomes of the study (preventative effects) are yet to be assessed.

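### The 144 randomised are judged against an intermediate figure of 134, although the plan's final requirement is 194; the stated 80% power does not describe the trial as run.

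*Protocol article*

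**What the plan says.** All the sizing is in the Protocol article, Sample size requirements and power calculation.

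- The assumed effects are "group differences of 0.45 SDs for continuous outcome measures" and "an odds ratio of 2.5 for case level depression". At alpha 0.05, 120 participants at follow-up "was estimated to provide 80 % power". Whether the test is one-sided or two-sided is not stated.
- The section says that power was first worked out as if for simple random sampling, and that the clustering adjustment came afterwards.
- On attrition: "Based on our previous experience, we conservatively estimated" 10% from baseline to follow-up. This turns 120 into 134, and of the 134 the text remarks that "this was close to the 144 individuals actually randomized".
- Later in the same paragraph the design effect of 1.44 is applied: "The final estimated required sample size at baseline adjusted for design effect and attrition was" 194. That number is converted to 21 schools, and the paragraph closes by reporting that 23 were screened.

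Trial status reports that "118 eligible participants in nine parallel groups have completed the interventions and pre/post assessments", with the two-year assessments still under way.

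**The concern.** By the section's own account, 134 is a halfway figure: it allows for attrition but not for the design effect. The achieved 144 exceeds it. The figure the plan calls final is 194, and 144 falls well below that. At the 194 step the only achieved number offered is the count of schools, which also looks favourable. The one comparison that would show a shortfall is not made.

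The main outcome is still to be assessed. A reader who meets a null result will set it against the stated 80% power. If the plan's own assumptions give appreciably less for the number randomised, that reading would be wrong.

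**Working it through.** **Inputs from the Protocol article.** 120 at follow-up; attrition 10%; mean cluster size 9.275; coefficient of variation (CV) of cluster size 0.25; intra-class correlation (ICC) 0.05; effect 0.45 SD; alpha 0.05; 144 randomised; 23 schools screened; 118 completers.

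**Assumptions.** 1:1 allocation: the document describes two arms allocated "using a minimisation method available in the MINIM program" and states no ratio. Both one-sided and two-sided tests are shown. Where the achieved cluster size is used, participants are spread over all 23 screened schools and CV and ICC are unchanged.

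**Step 1: reproduce the plan's figures.**
- Attrition: 120/0.90 = 133.3, rounded up to 134.
- Design effect: 1 + [(1 + CV²)m − 1] × ICC = 1 + [(1.0625 × 9.275) − 1] × 0.05 = 1.443, printed as 1.44.
- Final requirement: 134 × 1.443 = 193.3, rounded up to 194 (134 × 1.44 = 192.96; the difference is rounding).
- Schools: 194/9.275 = 20.9, so 21.

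Every printed figure reproduces. The fault lies in the comparison, not in the sums.

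**Step 2: compare the achieved number with each benchmark.**
- 144/134 = 107%.
- 144/194 = 74%; 194 − 144 = 50 short.

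**Step 3: allow for smaller clusters than planned.** 144/23 = 6.26 per school. Design effect = 1 + [(1.0625 × 6.26) − 1] × 0.05 = 1.28. Requirement = 134 × 1.28 = about 172. The gap narrows to about 28 and does not close.

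**Step 4: power for 0.45 SD.** Effective n = N/design effect. Power comes from the noncentral t distribution with noncentrality 0.45 × √(effective n/4). In the rows for achieved cluster size, the design effect is recomputed from N/23.

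| Analysed at two years | Design effect | Effective n | Two-sided | One-sided |
|---|---|---|---|---|
| 144 (no loss) | 1.44 | 100 | 0.61 | 0.72 |
| 144 (no loss) | 1.28 | 112 | 0.66 | 0.77 |
| 130 (10% loss) | 1.44 | 90 | 0.56 | 0.68 |
| 130 (10% loss) | 1.25 | 104 | 0.62 | 0.74 |
| 118 (if only completers are followed) | 1.44 | 82 | 0.52 | 0.65 |
| 118 (if only completers are followed) | 1.22 | 97 | 0.59 | 0.71 |

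No row reaches 0.80, including those with no loss at all.

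**Step 5: the completers.** (144 − 118)/144 = 26/144 = 18% had not completed the intervention and pre/post assessments.

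No equivalent table is given for the odds ratio of 2.5, because the article states no control-arm rate of depression.

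**The case against.** **The design effect may not belong here.** The section stresses that allocation is by individual, not by school. In that setting a full inflation of the treatment contrast is arguably too strict. This has force: with no design effect, about 130 followed gives 0.82 one-sided, though 0.72 two-sided. But the plan adopts 1.44, calls the result final and derives its school target from it. It cannot keep 194 as the requirement and judge recruitment against 134.

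**The text does not claim that the target was met.** This is fair. It says only that 134 and 144 are close, prints 194 openly and presents the calculation as a guide. A reader may infer from the favourable comparison that the trial reached its size; the words do not say so. What stands is that the relevant comparison is missing and the one supplied misleads.

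**A reader might infer that 118 already rules out the 120 needed at follow-up, or that it disproves the 10% attrition.** The document does not support either inference. The 118 counts people who finished the intervention and the pre/post assessments; the 120 counts people assessed at two years. The Two-year longitudinal follow-up section does not limit recontact to completers, and packs were posted to those who missed sessions. Some of the other 26 may still be assessed. The participant flowchart is not available here, so those 26 cannot be broken down.

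**A reader might also infer that 118 is underpowered even without a design effect.** That would confuse two issues. On a two-sided test the plan's own 120 gives only 0.69 (0.79 one-sided), and moving from 120 to 118 costs less than 0.01. That gap to 80% comes from the unstated sidedness, not from recruitment.

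**Conclusion.** The point holds and is wrong as written: 144 is compared with 134 when the plan's final baseline requirement is 194, a shortfall of 50 (26%). With the planned 10% loss, power for 0.45 SD is about 0.56 to 0.62 two-sided, or 0.68 to 0.74 one-sided, as the design effect goes from 1.44 to about 1.25. The stated 80% therefore does not describe the trial as run under the plan's own assumptions.

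This rests on 1:1 allocation, on the plan's CV and ICC, on all 23 screened schools contributing for the lower design effect, and on a design effect applying at all. The 18% non-completion suggests that 10% loss may be optimistic. It is not a two-year attrition rate.

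**What to change.** In Sample size requirements and power calculation, take one of two routes.

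1. Keep the design effect. Compare 144 with 194, state the shortfall of 50, and restate the expected two-year power as a range over the design effect (planned and achieved cluster size) and the follow-up number, with the sidedness of the test declared.
2. If 1.44 is judged inapplicable under individual allocation, say so with the reason, and withdraw both the 194 and the 21-school derivation. Then restate power for the number expected at follow-up, again with sidedness declared.

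On either route, leave the 10% attrition as the planning assumption. Report the 18% non-completion beside it, identified as completion of the intervention and pre/post assessments, and show power at both follow-up numbers (about 130 and 118).

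The cost is wording and a short recalculation. Recruitment is complete and nothing in the conduct of the trial changes; the stated power becomes less favourable on route 1, and on route 2 if the test is two-sided.
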